### Research aims and hypotheses

The overarching aim of this RCT is to assess the impact of a low-resource/low-intensity PSS-SRH integrated draft intervention package, augmented to existent health systems, on (1) the use of selected SRH services (specifically contraception/family planning use), and (2) the well-being of Syrian adolescent girls and young women refugees, by enhancing their self-efficacy and knowledge on said topics. This would include improving contraception/family planning use and well-being among the EG compared to the CG at 3 months-post intervention (T2).

This research study further aims to conduct a process evaluation to assess intervention fidelity and attrition during intervention implementation, as well as stakeholder satisfaction and key lessons learnt to inform global-scale up in different humanitarian settings.

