### Outcome measures

To thoroughly evaluate the impact and effectiveness of the intervention package, we will employ a comprehensive set of questionnaires (incorporating various tools) that will be administered to both the EG and CG. These questionnaires will enable the research team to thoroughly assess the impact of the intervention package on various aspects of the participants' lives, including their well-being and SRH. Refer to Table 1 for a detailed description of each tool and the time of administration.

**Table 1 T1:** Outcome evaluation tools and time of administration.

Outcome	Aim	Tool	Study period			
			Screening	Baseline T0	End-line T1 (8 weeks)	3 months post-intervention T2 (20 weeks)
Participant Inclusion	Inclusion and exclusion	Screening tool (24 questions)	X			
Primary outcome	At least 20% improvement in family planning use among the EG compared to the CG at three months.	Pan Arab-Family Health (PAPFAM) survey (24) (BL: 68 questions; EL: 35 questions; P3M: 37 questions)		X	X	X
Secondary outcomes	Improved well-being among the EG compared to the CG at three months. Multiple dimensions of well-being will be assessed.	Hopkins Symptom Checklist 25 (25 questions) (20, 25, 26)		X	X	X
		WHO-5 Wellbeing (5 questions) (27)		X	X	X
		General Self-Efficacy Scale (10 questions) (28)		X	X	X
		Multidimensional Scale of Perceived Social Support for Arab Women (12 questions) (29)		X	X	X
Intermediate outcomes	Improvement in important mediators in the EG compared to the CG	The Difficulties in Emotion Regulation Scale Short Form DERS-SF (18 question) (30, 31)		X	X	X
		Interpersonal Communication Competency scale (32) (17 question)		X	X	X
		Revised Ways of Coping Checklist (12 questions) (33)		X	X	X
Important variables and confounder	Such as socio-demographic factors; Family planning including other SRH knowledge; Women's reproductive and obstetric history; Gender disadvantage; and previous history of domestic violence	Using questions from the PAPFAM Survey (24).		X	X	X

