#### Intermediate outcomes

The intermediate outcomes will measure improvement in important mediators in the EG compared to CG at three months. Mediators include emotional regulation, communication skills, and coping, problem management and decision making.

Emotional regulation will be measured by the Difficulties in Emotion Regulation Scale Short Form (DERS-SF). The DERS-SF consists of 18-items, with participants rating their answers in the past week on a scale from 1 (almost never) to 5 (almost always). Total scores range from 18 to 90, with higher scores indicating more difficulty in emotional regulation (34).

Communication skills will be measured by the Interpersonal Communication Competency Scale (ICCS). The tool assesses ten dimensions of interpersonal communication competence (self-disclosure, empathy, social relaxation, assertiveness, alter-centrism, interaction management, expressiveness, supportiveness, immediacy, and environmental control. A total of 17 questions will be selected from the scale based on a study done in Brazil (32).

Coping, strategies, problem solving, and decision making will be assessed using the Revised Ways of Coping Checklist (RWCCL), which measures different types of coping will also be used. It will enable the research team to evaluate the structure of the interpersonal or individual social supports as well as their collective or networked social supports. The RWCCL is a widely used multidimensional coping measure with satisfactory reliability and validity (33, 36). Specific subscales were chosen based on our aim, and to avoid overlapping questions. The included subscales are: Confrontive coping, Escape-Avoidance, and Planful problem-solving.

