Analysis of secondary outcomes will be conducted at endline (T1) and 3 months post-intervention (T2) 1- to evaluate the potential increase in the secondary outcomes (well-being), and 2- in the use of the other SRH services associated with the intervention; 3- to investigate potential mediators of the primary comparison; 4- to investigate the effect of co-interventions and adherence. Mediators will be assessed as additional explanatory variables to the primary logistic regression models.

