## Discussion

Improving SRH and PSS knowledge coupled with skills-building around SRH self-efficacy is expected to improve selected SRH service use, mainly family planning use, which could ultimately lead to better SRH outcomes such as averting unplanned pregnancies, reducing complications of unsafe abortion, pregnancy, childbirth, and STIs among adolescent girls and young women refugees. Additionally, commensurate improvements in the secondary outcome, well-being, is also expected (37).

The developed intervention package is designed to be easily integrated into existing health systems, such as in routine PHC or social services settings at the national level, specifically in humanitarian settings effectively, efficiently, and in a culturally appropriate manner. This is in line with the WHO building block #1, as it could improve access and use of essential health services that are often compromised in humanitarian and fragile settings. The integration of SRH-PSS services at times of urgency and need is critical, given the scarcity of resources and the stringent abilities for continued and sustained health care for refugees and displaced populations in humanitarian settings (38).

In addition, it could lead to improved quality of care, as the integration of health services could yield more efficient use of health care resources, including human resources, community health care workers, and other paraprofessionals to deliver such service, in line with the WHO building block #2: empowering the health care workforce.

Finally, the findings of this research will provide potentially useful insights for the adaptation of the intervention package for young people in humanitarian contexts. This is essential in informing decisions of key stakeholders for broader dissemination and scale-up in humanitarian settings. The findings may also be useful for public health policymakers, as they could broaden the understanding of what works more effectively and for whom in fragile contexts.

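### The one stated mediation method, adding mediators to the logistic model, does not estimate an indirect effect, and the named mediators omit knowledge and self-efficacy, the mechanism given in the trial's aim

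*Protocol article*

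**What the plan says.** The Analysis section lists the investigation of potential mediators of the primary comparison among the secondary analyses at T1 and T2, and gives the method in one sentence: "Mediators will be assessed as additional explanatory variables to the primary logistic regression models". The primary models are separate multivariable logistic regressions for T0-T1 and T0-T2 that give odds ratios of FP use.

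The Intermediate outcomes section names the mediators: "Mediators include emotional regulation, communication skills, and coping, problem management and decision making". It adds: "The intermediate outcomes will measure improvement in important mediators in the EG compared to CG at three months".

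The Research aims section says the package should act on service use and well-being "by enhancing their self-efficacy and knowledge on said topics". The Discussion repeats this: "Improving SRH and PSS knowledge coupled with skills-building around SRH self-efficacy is expected to improve selected SRH service use".

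Table 1 (Outcome measures) places the General Self-Efficacy Scale under secondary outcomes. It places "Family planning including other SRH knowledge" in the row headed "Important variables and confounder". The mediator scales, the self-efficacy scale and that row are all marked at T0, T1 and T2.

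**The concern.** There are two problems.

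1. **Method.** Entering a mediator as a covariate invites the reader to interpret either the shift in the arm odds ratio or the mediator's own coefficient. Neither is an indirect effect. The odds ratio moves away from 1 when any predictor of FP use is added, even one the intervention does not touch. Randomisation protects the arm comparison but not the mediator-outcome relation, so a shared cause of mediator and FP use also distorts the result.
2. **Choice of mediators.** The aims and the Discussion both say the package works through knowledge and self-efficacy, and neither is among the named mediators.

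The explanation of how the package works is at stake. The Discussion intends the findings to inform adaptation and scale-up. A wrong or missing account of the mechanism could steer which modules are kept.

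**Working it through.** **Inputs.** From Sample size: 30% control and 50% intervention FP use at three months. The plan's relative risk reproduces: 0.50/0.30 = 1.67. The matching odds ratio is (0.50/0.50)/(0.30/0.70) = 2.33, with log 0.847. The plan gives no mediation figure and no mediator strength. Strengths of g = 0.3, 0.5, 1.0 and 1.5 log-odds per SD are assumptions (odds ratios of 1.35, 1.65, 2.72 and 4.48 per SD).

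**Step 1: no mediation.** M predicts FP use but has the same N(0,1) distribution in both arms. The model is logit P(Y=1) = a_arm + g·M. Each a_arm is solved by numerical integration so that the marginal rates are 30% and 50%. This gives a = 0 in the EG. Apparent share = 1 − (adjusted log OR)/0.847.

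| g | a in CG | adjusted OR | apparent share (truth 0) |
|---|---|---|---|
| 0.3 | −0.865 | 2.37 | −2% |
| 0.5 | −0.895 | 2.45 | −6% |
| 1.0 | −1.018 | 2.77 | −20% |
| 1.5 | −1.188 | 3.28 | −40% |

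**Step 2: true mediation, no confounding.** The arm shifts M by 0.4 SD, with a direct log OR of 0.55 (both assumed). The control rate is held at 30%, so the intervention rate p1 follows from the model and comes close to 50% only for strong mediators. p10 is the rate under intervention with M left at its control distribution. True share on the risk-difference scale = (p1 − p10)/(p1 − 0.30). Read share = 1 − 0.55/(log total OR).

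| g | p1 | p10 | total OR | true share | read share |
|---|---|---|---|---|---|
| 0.3 | 45.2% | 42.4% | 1.93 | 19% | 16% |
| 0.5 | 46.6% | 41.9% | 2.03 | 28% | 23% |
| 1.0 | 48.6% | 40.4% | 2.21 | 44% | 30% |
| 1.5 | 49.3% | 38.9% | 2.27 | 54% | 33% |

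**Step 3: confounding** (1,000,000 simulated records, 30% vs 50%). The arm moves M by 0.5 SD. An unmeasured cause is correlated 0.6 with M and acts on FP use with log-odds 1.0.
- If M has no effect on FP use, the arm OR still falls from 2.33 to 1.88, a false 25% mediated.
- If M does act (g = 1.0), a true 40% reads as 47%. Here the error is upward.

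**Step 4: reading the mediator's coefficient instead.** Suppose FP use itself raises a same-visit M by 0.5 or 1.0 SD, and M causes nothing. The arm difference in M is 0.5 × 0.20 = 0.10 SD or 1.0 × 0.20 = 0.20 SD. The coefficient of M in the logistic model is 0.50 or 1.00. M looks related to both arm and outcome without mediating anything.

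**Step 5: mediator list against stated mechanism.**

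| Construct | Research aims, Discussion | Intermediate outcomes | Table 1 |
|---|---|---|---|
| Knowledge | mechanism | not named | important variables and confounder |
| Self-efficacy | mechanism | not named | secondary outcome |
| Emotion regulation, communication, coping | not named individually | mediators | intermediate outcomes |

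**The case against.** The strongest reply is that the protocol promises no mediated share, that the distortion is small for weak mediators (−2% against 0, or 16% against 19%, at g = 0.3), and that details belong in the analysis plan. The point about weak mediators stands. The rest only partly answers the concern: the sentence states a method and does not leave it open, and neither number that method produces is an indirect effect.

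A reader might infer four stronger points that the protocol does not support:

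- **Mediators are taken at the same visit as the outcome.** The three-month statement under Intermediate outcomes describes an arm comparison of the mediators. In the T0-T1 model the only post-baseline value is the same-visit one. For T0-T2, however, T1 values are scheduled and the text does not say which visit enters. Step 4 is thus a risk under one reading, not a consequence of a written rule.
- **Post-baseline knowledge will be adjusted for as a confounder, removing part of the effect.** The row label is mixed, balance is checked on baseline variables, and the models are said to adjust for sociodemographic confounders. Adjustment for later knowledge is nowhere prescribed.
- **The stated mechanism will not be tested.** The list says only that mediators include those named, and being a secondary outcome does not bar self-efficacy. The mismatch needs clearing up, but it excludes neither construct.
- **The trial cannot show how the package works, or mediation will always be understated.** The scheduled data could support a proper analysis, and Step 3 shows error in the other direction.

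**Conclusion.** The point holds in a limited form. The one mediation method stated does not quantify an indirect effect, and the named mediators do not match the mechanism in the aims and Discussion.

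The size depends on assumed mediator strengths. It runs from negligible at 0.3 log-odds per SD to serious at 1.0 and above. True shares of 19% to 54% also assume a 0.4 SD shift, a direct log OR of 0.55 and no confounding. With confounding, the direction of error is not predictable.

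The primary comparison, the sample size and the type I error are untouched. This is a minor-to-moderate point about a secondary, explanatory analysis.

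**What to change.** Replace the sentence on mediators in the Analysis section with an analysis labelled exploratory that:

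- uses mediator values at T1 and FP use at T2;
- adjusts for the T0 mediator, T0 FP use, site and baseline mediator-outcome confounders;
- reports direct and indirect effects on the risk-difference scale with bootstrap confidence intervals;
- adds a sensitivity analysis for unmeasured mediator-outcome confounding, and for confounders that the intervention itself affects, including T1 FP use and the other mediators.

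Add General Self-Efficacy to the mediator list. Add FP/SRH knowledge too, provided its items remain in the shortened endline questionnaire (Table 1 shows 68 PAPFAM questions at baseline and 35 at endline, without saying which are kept). State that only T0 values of the Table 1 confounders enter the effect models.

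The cost is rewording and some extra analysis, with no new visits. The price is reliance on identification assumptions that randomisation does not guarantee. These should be stated with the results, because treatment-affected confounders mean that single-mediator effects are not identified without them.

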## Discussion

Improving SRH and PSS knowledge coupled with skills-building around SRH self-efficacy is expected to improve selected SRH service use, mainly family planning use, which could ultimately lead to better SRH outcomes such as averting unplanned pregnancies, reducing complications of unsafe abortion, pregnancy, childbirth, and STIs among adolescent girls and young women refugees. Additionally, commensurate improvements in the secondary outcome, well-being, is also expected (37).

The developed intervention package is designed to be easily integrated into existing health systems, such as in routine PHC or social services settings at the national level, specifically in humanitarian settings effectively, efficiently, and in a culturally appropriate manner. This is in line with the WHO building block #1, as it could improve access and use of essential health services that are often compromised in humanitarian and fragile settings. The integration of SRH-PSS services at times of urgency and need is critical, given the scarcity of resources and the stringent abilities for continued and sustained health care for refugees and displaced populations in humanitarian settings (38).

In addition, it could lead to improved quality of care, as the integration of health services could yield more efficient use of health care resources, including human resources, community health care workers, and other paraprofessionals to deliver such service, in line with the WHO building block #2: empowering the health care workforce.

Finally, the findings of this research will provide potentially useful insights for the adaptation of the intervention package for young people in humanitarian contexts. This is essential in informing decisions of key stakeholders for broader dissemination and scale-up in humanitarian settings. The findings may also be useful for public health policymakers, as they could broaden the understanding of what works more effectively and for whom in fragile contexts.
